|  | **Multiple (≥2) metformin scripts filled (N=637)** | **Metformin unexposed**  **N= 2,672** | **Crude RR**  **(95% CI)** | **Inverse probability weighted RR (95% CI)** |
| --- | --- | --- | --- | --- |
| Hypertensive disorders of pregnancy | 43 (6.8) | 209 (7.8) | 0.86 (0.63-1.18) | 0.96 (0.61-1.49) |
| Preeclampsia | 18 (2.8) | 77 (2.9) | 0.98 (0.59-1.63) | 0.96 (0.47-1.95) |
| Preterm preeclampsia <37/40 | 4 (0.6) | 30 (1.1) | 0.47 (0.16-1.39) | 0.56 (0.18-1.73) |
| Pregnancy-induced hypertension | 25 (4.0) | 132 (5.1) | 0.79 (0.52-1.21) | 0.96 (0.53-1.75) |

**Additional File 1: Analysis plan for investigating associations between metformin use in pregnancy and preeclampsia among women with diabetes**

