**Null hypothesis**

Taking metformin during pregnancy does not affect the likelihood of developing preeclampsia among women with diabetes.

1. **Background**

Metformin is an oral hypoglycaemic agent prescribed to women in pregnancy with pre-existing Type II diabetes and gestational diabetes. It has well-described benefits for mother and neonate when used in this context [22]. Beyond diabetes, metformin has been reported to reduce the likelihood of pregnancy complications among women with polycystic ovary syndrome [23, 24], and in women with previous unsuccessful attempts at in vitro fertilisation (IVF) [25].

Compared with insulin, two meta-analyses concluded that metformin administration is associated with lower rates of preeclampsia[22], and pregnancy-induced hypertension [8]. However, in women with diabetes, studies in this area have been small. Population-based research with larger numbers could generate stronger evidence to better investigate this relationship.

The objective of this research is to determine the relationship between metformin and hypertensive disorders of pregnancy (preeclampsia, eclampsia, gestational hypertension) among women with diabetes, using a national population-based cohort from Scotland.

1. **Study population**

The population will include all nulliparous singleton pregnancies with a diagnosis of diabetes (gestational diabetes or Type II diabetes), recorded in the Scottish Morbidity Records between 2009 and 2018. The Scottish Morbidity Records hold data relating to pregnancy, delivery and perinatal outcomes for all women and infants discharged from maternity hospitals across Scotland.

Exclusion criteria:

a) Multifetal pregnancy

b) Parous women (to account for clustering)

c) Missing gestational age (which will be used to calculate gestational age at exposure)

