**Exposure**

Maternal metformin use during pregnancy will be identified through the Scottish National Prescribing Information System (PIS), which has been linked with the Scottish Morbidity Records. Metformin use will be further categorised as use ever, 0 – 12 weeks, 13 – 27 weeks, and 28 weeks onward. Metformin exposure will be assessed for timing, with only prescription prior to preeclampsia diagnosis included.

1. **Primary outcomes:**

Diagnosis of preeclampsia identified by codes O11, O14 and O15 according to the International Classification of Disease Tenth Revision.

Preeclampsia will be further classified by stratifying according to gestational age at birth; <37 weeks and <34 weeks.

Secondary outcomes:

- Gestational hypertension ICD-O13
- Neonatal birthweight: small for gestational age at birth or large for gestational age at birth (defined according to **1)** < or > 2 SD; adjusted for gestational age and offspring sex or **2)** birthweight centile calculated using GROW charts; <10^th^ percentile for SGA and >90^th^ percentile for LGA) (binary)
- Macrosomia; birthweight >4500g (binary)
- Neonatal intensive care unit admission (obtained via neonatal indicator variable)
- Major congenital abnormality (binary)
- Congenital renal anomaly (binary)
- Perinatal death (binary)
- Preterm birth

1. **Additional analyses:**

- Metformin exposure for any indication, compared to the total unexposed population (whether or not they were diagnosed with diabetes)
- It is anticipated that most women requiring metformin in pregnancy will have been prescribed this in the context of Gestational Diabetes or Type II diabetes. The main analysis has therefore been limited to diabetic women, to eliminate diabetes as a confounder
- By number of scripts filled for metformin (possibly reflects compliance)
- By dose, categorised as 1g and >1g

1. **Outline of statistical analysis**
   1. Descriptive analysis

Summary statistics of baseline characteristics of patients will be presented with mean (SD) used to describe normally distributed continuous variables, median (IQR) for skewed continuous variables, and n (%) for categorical variables. Univariate analyses will be performed for each of the variables of interest to be included in the model.

Population characteristics to be described for:

a) Overall cohort

b) Metformin exposed vs non-exposed cohort

| Characteristic | Descriptor | Total population | Metformin exposed | Metformin unexposed |

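### The planned analysis by number of metformin scripts cannot isolate compliance, because the raw count also depends on when treatment started, when counting stopped and how long each supply lasts

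*SAP*

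**What the plan says.** The analysis plan (SAP, Additional File 1, Exposure) takes metformin use from linked prescribing records and classifies it as "use ever, 0 – 12 weeks, 13 – 27 weeks, and 28 weeks onward". Timing is to be assessed, "with only prescription prior to preeclampsia diagnosis included". Gestation at exposure will be derived, because one exclusion under Study population is "Missing gestational age (which will be used to calculate gestational age at exposure".

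Under Additional analyses the plan lists "By number of scripts filled for metformin (possibly reflects compliance" and, as a separate item, "By dose, categorised as 1g and >1g". The script-count item gives no cut-off, no time denominator and no reference to quantity or days' supply. Compliance is the only purpose it states.

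Table S4 reports one analysis of this kind. Its exposed column is headed "Multiple (≥2) metformin scripts filled (N=637" and its comparator is 2,672 unexposed women. Women with exactly one script are in neither column. The table's title refers to metformin use with multiple scripts and does not mention compliance.

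**The concern.** Compliance is the share of intended treatment that was taken. A script count is a numerator without a denominator. Two women with the same adherence will have different counts if one starts earlier, is delivered or diagnosed later, or receives shorter supplies.

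This cohort makes the problem likely to matter. It pools gestational diabetes, which arises during pregnancy, with pre-existing Type II diabetes, where metformin may already be in use at conception. The plan itself anticipates starts in all three periods of pregnancy. A ranking by script count can therefore track early versus late indication. Counting stops at preeclampsia diagnosis, so an early diagnosis also lowers the count whatever the adherence. The plan does not cross script count with gestation at start or with dose.

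A difference between script-count groups, or the lack of one, therefore could not be read as an effect of taking metformin more or less faithfully.

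**Working it through.** **The plan's own figure.** Table S4, preeclampsia: 18 of 637 women with at least two scripts against 77 of 2,672 unexposed.

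- RR = (18/637) / (77/2,672) = 0.02826 / 0.02882 = 0.981.
- SE of log RR = √(1/18 − 1/637 + 1/77 − 1/2,672) = 0.258.
- 95% CI = 0.981 × exp(±1.96 × 0.258) = 0.591 to 1.626.

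This matches the printed crude RR of 0.98 (0.59–1.63). The rows for hypertensive disorders, 0.86 (0.63–1.18), and pregnancy-induced hypertension, 0.79 (0.52–1.21), also reproduce. The preterm preeclampsia row does not: 4/637 against 30/2,672 gives 0.56 (0.20–1.58), where 0.47 (0.16–1.39) is printed. That is a separate matter and does not bear on this point.

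**Assumptions for the illustration (none is in the SAP).** Birth at week B = 38, range 37 to 40. Days' supply per script d = 28 or 56, with 84 as a further case. Each script is refilled when the supply runs out.

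**Scripts filled** = 7 × (B − start week) × adherence / d, rounded up.

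| Start | Adherence | Days' supply needed | 28-day scripts | 56-day scripts |
|---|---|---|---|---|
| Week 8 | full | 7 × 30 = 210 | 7.5 → 8 | 3.75 → 4 |
| Week 26 | full | 7 × 12 = 84 | 3 | 1.5 → 2 |
| Week 34 | full | 7 × 4 = 28 | 1 | 0.5 → 1 |
| Week 8 | half | 210 / 2 = 105 | 3.75 → 4 | 1.875 → 2 |

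The first three rows have identical adherence and counts from 8 down to 1. The last row shows that on 28-day supplies a half-adherent early starter (4) ranks above a fully adherent week-26 starter (3). On 56-day supplies the two tie at 2. The inversion is thus not general, but in neither case does the count rank the two women correctly.

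**Who falls outside the two-script group.** A fully adherent woman fills one script only if her start week is at least B − d/7.

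- B = 38: from week 34 (28-day), week 30 (56-day) or week 26 (84-day).
- B = 37 to 40: from week 33–36, 29–32 or 25–28 respectively.

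The SAP gives neither the number of single-script women, nor their gestation at start, nor the supply length. How many women the rule leaves out for this reason cannot be computed.

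**Check of the replacement.** Proportion of days covered = days' supply dispensed / days from first script to diagnosis or birth, capped at 1.

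- Half-adherent week-8 starter: 4 × 28 / 210 = 0.53, or 2 × 56 / 210 = 0.53.
- Fully adherent week-26 starter: 3 × 28 / 84 = 1, or 2 × 56 / 84 = 1.33, capped at 1.

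The measure separates the two women under both supply lengths, which the count does not.

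**The case against.** The strongest reply is that the plan claims little. It says only that the count possibly reflects compliance, in one line of a list of additional analyses, and it specifies no trend or dose-response test on the count. Timing and dose each have their own analysis. Table S4 makes no compliance claim, and its cut-off of two scripts does not come from the plan line. Most of this stands, and it rules out several stronger readings that a reader might infer:

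- **That the plan adopts the count as its measure of compliance.** The wording is hedged.
- **That the count mainly reflects start and pack size.** The SAP has no figures on start weeks, supply lengths or adherence, so their relative contributions are unknown.
- **That Table S4 treats single-script women as non-compliers, or drops late starters in general.** It applies no such label. On the assumptions above a week-26 starter stays in; only late starters with a single script fall out.

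It is also fair to say that gestation at first script does not exist for the unexposed women. Its absence from the covariate list under Outcome analysis is therefore not an error, and it could not simply be added to the Table S4 comparison.

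The defect remains. The hedge supplies no denominator, and separate analyses by timing and dose do not remove their influence on an analysis by count. Compliance is the one reason given for that analysis.

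**Conclusion.** The point holds as a limited one. The analysis by number of scripts cannot isolate compliance, because the count mixes it with gestation at first script, time to diagnosis or birth, and days' supply. At full adherence and birth at 38 weeks the count runs from 8 to 1 on 28-day supplies and from 4 to 1 on 56-day supplies for starts between weeks 8 and 34. These figures rest on assumed supply lengths and birth week; the direction does not.

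It follows that the near-null preeclampsia result in Table S4 (crude RR 0.98, weighted 0.96) does not show whether better adherence changes risk. A reader might go further and infer that the result is biased by a known amount, or that the main finding is in doubt. The documents support neither: the number of women affected is not given, and the primary comparison of exposed with unexposed women does not use the count. This is a worthwhile, inexpensive improvement to a secondary analysis.

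**What to change.** - **Replace the measure.** For the compliance question, among metformin-exposed women only, use proportion of days covered: days' supply dispensed divided by days from first script to outcome diagnosis or birth, capped at 1.
- **Fallback.** If quantity is not held, use scripts per week from first script. This is weaker, because it still depends on supply length: 4/30 = 0.13 per week describes both a half-adherent week-8 starter on 28-day supplies and a fully adherent one on 56-day supplies.
- **Start of treatment.** Stratify by, or adjust for, gestation at first script within the exposed women.
- **Single-script women.** Report their number and outcomes by gestation at start, next to Table S4.
- **Wording.** Keep the script count as descriptive and remove the compliance reading from the Additional analyses item.

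The cost is a change of SAP wording and one derived variable. Gestation at exposure is already to be derived, and the planned analysis by dose implies that some dose information is available. The SAP does not say that quantity or days' supply is held, so a daily-dose assumption will be needed where directions or quantity are missing.

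One limit should be stated in the plan. A woman whose time from first script to diagnosis or birth is shorter than one supply is fully covered by construction, so for her the measure says nothing about adherence. Nor does it remove the need to remain undiagnosed until a second script is filled; that is a separate question.

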**Table S2: Covariate balance: Standardized differences**

|  | | **Scotland cohort** | | **Sweden cohort** | |
| --- | --- | --- | --- | --- | --- |
|  |  | **Raw** | **Weighted** | **Raw** | **Weighted** |
| **Maternal age >35 years** | | 0.16 | -0.09 | 0.07 | -0.11 |
| **Smoking during pregnancy** | | -0.01 | 0.17 | -0.05 | 0.06 |
| **Body mass index >30kg/m^2^** | | 0.21 | -0.14 | 0.48 | 0.03 |
| **Year of delivery** | | 0.84 | -0.02 | 0.78 | -0.07 |
| **Maternal education** | | N/A | | -0.11 | -0.04 |
| **IVF pregnancy** | | N/A | | 0.03 | -0.06 |
| **Country of birth** | | N/A | | 0.14 | 0.02 |
| **Pre-existing medical condition** (chronic hypertension, renal disease, systemic lupus erythematosus) | | N/A | | -0.01 | -0.01 |
| **Chronic hypertension** | | 0.03 | -0.05 | N/A | |
| **Polycystic ovary syndrome** | | 0.07 | -0.03 | N/A | |
| **Socioeconomic status (quintiles)** | **2** | 0.02 | 0.11 | N/A | |
|  | **3** | 0.05 | 0.01 |  |  |
|  | **4** | -0.10 | 0.04 |  |  |
|  | **5** | 0.00 | -0.03 |  |  |

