| --- | --- | --- | --- | --- |
| **Age,** (years) | mean ±SD |  |  |  |
| **Age >35 years** | n (%) |  |  |  |
| **Body mass index** (kg/m^2^) | mean ± SD |  |  |  |
| **Body mass index >30mg/kg** | n (%) |  |  |  |
| **Ethnicity** | n (%) |  |  |  |
| **Smoking,** yes | n (%) |  |  |  |
| **Deprivation score**  1  2  3  4  5 | n (%) |  |  |  |
| **Pre-gestational disorders**  Hypertension  Cardiovascular disease  Autoimmune diseases  Diabetes  Type I  Type II  Renal disease | n (%) |  |  |  |
| **Year of birth**  2009  2010  2011  2012  2013  2014  2015  2016  2017  2018 | n (%) |  |  |  |
| **Gestational diabetes** | n (%) |  |  |  |

- 1. **Outcome analysis**

Potential estimators are (i) selection model, using inverse probability weighting (IPW); (ii) outcome model, using regression adjustment; (iii) doubly robust inverse probability weighted regression adjustment (IPWRA) models. Under correct specification, all the estimators should produce similar results. We will focus on IPWRA; selection model will be included in the IPW and outcome in regression (RA) model specification. We will combine both regression adjustment and augmented IPW in a doubly robust regression model. We will also perform RA, IPW and multivariate LR separately.

Model for exposure assignment using inverse probability weighted propensity scores derived from the logistic exposure model. Adequacy of balance achieved by PS weighting will be assessed using: (i) standardised mean difference for model covariates and variance estimates between exposure groups and (ii) propensity scores overlap. If unbalanced, we will explore measures such as: addition of interaction terms; different exposure models; use of alternate weighting structures (overlap or stabilized); and lastly propensity score-based trimming with the aim of achieving overlap if the propensity score distributions.

This will be performed for the overall cohort and then subgroup analyses will be performed.

The model will be created for each outcome with the final included covariates determined by the authorship team and informed by direct acyclic graphs (Fig S1, S2). Covariates to be considered:

1. Maternal age at delivery
2. Body mass index
3. Deprivation score
4. Ethnicity
5. Smoking status
6. Pre-existing maternal disease
7. Conception with assisted reproduction

All statistical analysis will be performed using StataSE version 17.0.

- 1. Handling of missing data

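### The plan acts on covariate imbalance without defining it; weighting leaves Scottish smoking at 0.17 and BMI >30 at -0.14, and Table S4 omits the planned IPWRA estimate

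*SAP*

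**What the plan says.** In the SAP's Outcome analysis section, exposure is modelled by logistic regression and the cohort is weighted by the propensity score. Balance is then to be checked: "Adequacy of balance achieved by PS weighting will be assessed using: (i) standardised mean difference for model covariates and variance estimates between exposure groups", together with overlap of the propensity scores. No value is given at which a covariate counts as unbalanced. The response is "If unbalanced, we will explore measures such as: addition of interaction terms; different exposure models; use of alternate weighting structures (overlap or stabilized", and trimming on the propensity score comes last. Apart from that, no order of remedies and no stopping rule is given.

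The same section names its lead estimator: "We will focus on IPWRA". It also plans regression adjustment, IPW and multivariable logistic regression as separate analyses. The section on missing data has IPWRA calculated in each imputed dataset and pooled by Rubin's rule.

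Table S2 gives standardised differences before and after weighting, in the order Scotland raw, Scotland weighted, Sweden raw, Sweden weighted. Two rows read "Smoking during pregnancy | | -0.01 | 0.17 | -0.05 | 0.06" and "Body mass index >30kg/m^2^ | | 0.21 | -0.14 | 0.48 | 0.03". The deprivation rows, for Scotland only, begin "Socioeconomic status (quintiles) | 2 | 0.02 | 0.11".

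Table S4 covers women with two or more metformin scripts. Number of scripts is listed in the SAP under Additional analyses. The adjusted column of Table S4 is headed "Inverse probability weighted RR (95% CI)", and there is no IPWRA column.

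**The concern.** A rule that starts with a condition but does not define it leaves the decision to whoever looks at the weighted table. Nothing in the text requires that decision to be made before outcomes are seen. Two analysts could read Table S2, one calling it balanced and the other not, and both would be following the plan.

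The table makes this a practical matter. Smoking and deprivation quintile 2 were balanced in the raw Scottish data and are less balanced after weighting. BMI >30 changes sign and keeps two thirds of its size (0.14/0.21 = 0.67). Age and BMI are to be described as means with SD, but their balance is shown only as >35 and >30, so imbalance within those categories is not visible.

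The planned safeguard against such residuals is the outcome model inside IPWRA. In the only effect table in the document, that estimate does not appear.

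**Working it through.** **1. Table S4 crude figures.** Inputs: 637 exposed and 2,672 unexposed women, with preeclampsia in 18 and 77.

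RR = (18/637)/(77/2672) = 0.981.

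SE of log RR = sqrt(1/18 - 1/637 + 1/77 - 1/2672) = 0.258.

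95% CI = 0.981 × exp(±1.96 × 0.258) = 0.59 to 1.63. The printed 0.98 (0.59-1.63) is reproduced. The rows for hypertensive disorders (43 vs 209) and pregnancy-induced hypertension (25 vs 132) also reproduce. Preterm preeclampsia (4 vs 30) does not: the counts give 0.56 (0.20-1.58), and the table prints 0.47 (0.16-1.39).

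**2. Variance after weighting.** Ratio = [ln(U/L) weighted / ln(U/L) crude]², from the printed limits. The range allows for rounding to two decimals.

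| Outcome | Weighted ln(U/L) | Crude ln(U/L) | Ratio | Range |
| --- | --- | --- | --- | --- |
| Hypertensive disorders | ln(1.49/0.61) = 0.893 | ln(1.18/0.63) = 0.628 | 2.03 | 1.90-2.16 |
| Preeclampsia | ln(1.95/0.47) = 1.423 | ln(1.63/0.59) = 1.016 | 1.96 | 1.88-2.04 |
| Pregnancy-induced hypertension | ln(1.75/0.53) = 1.194 | ln(1.21/0.52) = 0.845 | 2.00 | 1.90-2.11 |
| Preterm preeclampsia | ln(1.73/0.18) = 2.263 | ln(1.39/0.16) = 2.162 | 1.10 | 1.03-1.16 |

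A ratio of 2 means about half the information remains. For preterm preeclampsia, using the SE from the counts instead of the printed crude interval gives (0.5773/0.5305)² = 1.18, so that row is well short of doubling either way.

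**3. Table S2 against possible limits.** The SAP gives none, so these are assumed.

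| Absolute limit | Scottish rows above it, of 10 |
| --- | --- |
| 0.10 | smoking 0.17, BMI >30 -0.14, quintile 2 0.11 |
| 0.15 | smoking |
| 0.20 | none |

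Four Scottish rows have a larger absolute difference after weighting: smoking, chronic hypertension (0.03 to -0.05), quintile 2 and quintile 5 (0.00 to -0.03).

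The mean absolute difference over the 10 rows falls from 1.49/10 = 0.149 to 0.69/10 = 0.069. Without year of delivery it is (1.49 - 0.84)/9 = 0.072 before and (0.69 - 0.02)/9 = 0.074 after. The average gain is thus due to year of delivery; the other nine rows together are no better balanced than before.

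**4. Possible size of residual bias.** Prevalences and risk ratios are assumptions; the documents give none. For a binary confounder with prevalences p1 and p0 and outcome risk ratio R, the bias factor is [1 + p1(R - 1)]/[1 + p0(R - 1)].

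- Smoking alone: 21.5% vs 15% is a standardised difference of 0.065/sqrt[(0.215×0.785 + 0.15×0.85)/2] = 0.17. With R = 0.5 the factor is 0.8925/0.925 = 0.96. With R = 2.0 it is 1.215/1.15 = 1.06.
- Smoking and BMI >30 together: assume that differences are exposed minus unexposed, that BMI >30 prevalence is 40-60% with R 1.5-2.5, and that smoking prevalence is 10-15% with R 0.60-0.75. The joint factor is then 0.91-0.96. If the sign convention is the opposite, it is roughly the reciprocal, 1.04-1.10.

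**The case against.** The strongest reply is that the plan is better than this point makes it look. It names three balance checks and several remedies, and it makes a doubly robust estimator the lead. Weighting also did its largest job well, taking Scottish year of delivery from 0.84 to -0.02; removing so large an imbalance normally costs precision. All of this stands. It narrows the criticism of the plan to the missing limit and the missing order of remedies.

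Three stronger readings are tempting, and the documents do not support them.

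- **That Table S2 fails the plan's balance check.** There is no limit for it to fail. The result depends on the cut-off chosen, and at 0.20 every row passes. The document also does not say whether Table S2 shows first-pass weights or weights after remedies were tried.
- **That IPW was reported instead of IPWRA.** Separate IPW is a planned analysis, Table S4 is an additional analysis, its column label may be shorthand, and the main results (Tables 2 and 3, cited in the STROBE checklist) are not shown. What can be said is that Table S4 does not show the lead estimator or explain its absence.
- **That unstable weights doubled the variance, or that the residuals favour metformin.** The doubling is seen in three rows of four. No weight distribution or effective sample size is given, and pooling over imputations may contribute. Table S2 does not state its sign convention or whether exposure is any script or two or more, so its differences cannot be tied firmly to the Table S4 intervals.

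The Swedish column, including age >35 at -0.11, lies outside the analysis plan shown, which defines a Scottish cohort. The point does not rely on it.

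**Conclusion.** The concern holds in limited form. The SAP fixes no limit for imbalance, and its own weighted Scottish table falls where that omission matters: three of 10 rows are above 0.10, one is above 0.15 and none is above 0.20. Two of those three, smoking and deprivation quintile 2, were balanced until weighting was applied. Table S4 does not show the estimate that the plan relies on to deal with such residuals.

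The numerical consequence is probably modest. Under the assumed prevalences and risk ratios, the bias factor for smoking and BMI together is 0.91-0.96, or roughly its reciprocal if the sign is reversed. Dividing the weighted preeclampsia risk ratio of 0.96 by 0.96 and by 0.91 gives 1.00 and 1.05, well inside 0.47-1.95. The shift is comparable with the distance of 0.96 from 1, but it does not change a reading of no demonstrated effect. The direction cannot be determined from the documents. The loss of about half the information on preeclampsia, the primary outcome, should be explained. This is something the sponsor should correct; it does not invalidate the result.

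**What to change.** In the Outcome analysis section:

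1. State a limit: an absolute standardised difference of at most 0.10 for every covariate level, judged before outcomes are analysed. Check age and BMI as continuous variables as well as dichotomised.
2. Put the remedies already listed into a fixed order with a stopping rule, for example respecifying the exposure model, then overlap weights, with trimming still last. With a logistic propensity model, overlap weights balance every included covariate exactly. Their downside, to be stated, is a changed target population: women who could plausibly have received either option.
3. Report the effective sample size by exposure group for each weighted analysis.

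In the tables:

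4. Show IPWRA, with smoking, BMI and deprivation in the outcome model, as the lead estimate beside IPW in Table S4.
5. State in Table S2 the exposure definition, the sign convention, and whether remedies had already been applied.
6. Correct or explain the crude preterm preeclampsia risk ratio in Table S4.

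The cost is SAP wording and a re-run, with no new data. Because Table S4 already shows outcome results, a limit set now is not prespecified for those analyses, and the revised results should be labelled accordingly.
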